## Methods

### Design

This study is a non-randomized observational prospective case control study in a multicenter setting assessing the difference in sexual function between women with and without PCOS. Additionally, we examine the effect of OCP use resulting in a 2×2 design. The duration of the study will be 4 years. 3 Dutch academic medical centers will participate in this study: Erasmus Medical Center Rotterdam, Leiden University Medical Center (LUMC), and Amsterdam University Medical Center (AMC). Independent variables are PCOS status and OCP use. The dependent variables are sexual function as assessed with questionnaires and genital and self-reported sexual arousal in a laboratory setting.

Ethical approval was awarded by the Ethics Committee of Erasmus Medical Center, Rotterdam, The Netherlands (MEC 2016-216, NL55484.078.16). Local ethical approval was awarded by the Ethics Committees of LUMC (P16.299) and AMC (2016_182/NL55484.078.16).

### Participant Recruitment and Selection

Women who have been diagnosed with PCOS at the outpatient clinic of the Erasmus University Medical Center will be asked to participate in this study. Also, Dutch patient societies will be requested to advertise for our study. PCOS will be diagnosed according to the Rotterdam criteria.

An age-matched control group of healthy women will be recruited through advertisements in local newspapers, social media, or flyers at the outpatient gynecological clinics of Erasmus University Medical Center, LUMC, and AMC. Control women will also be recruited through the pool of volunteers available at LUMC. In the control group, women with PCOS will be excluded. In case PCOS is diagnosed, data will be used in the PCOS arm.

Inclusion criteria for participation are healthy women with a diagnosis of PCOS, healthy women without another diagnosis concerning the menstrual cycle, women aged between 18 and 40 years, and those with a stable heterosexual relationship for at least 6 months. Due to the nature of the erotic film material and the sexuality questionnaires, only heterosexual women are eligible.

Medical screening involves endocrine screening, assessment of BMI, a menstrual cycle history, a modified Ferriman-Gallwey score, and a transvaginal ultrasound in order to assess the ovarian morphology, antral follicle counts, and ovarian volumes of both ovaries. Total endometrial thickness will also be recorded as well as uterine sizes. The diagnosis of PCOS or of a normal menstrual cycle will be made after a standardized initial examination is performed between 07:45 and 10:00 am after an overnight fast in the early follicular phase of the menstrual cycle (third to fifth day of menses when no hormonal contraception is used) in case of a regular menstrual cycle. In case of a cycle irregularity, the examination will be performed on a random cycle day. In case of OCP use, screening will be on the eighth day of a new cycle after 7 days of not using OCPs. Endocrine features combined with medical screening will determine the diagnosis.

We will recruit women with PCOS and healthy women both either not using hormonal contraceptives (for at least 3 months prior to the start of their participation in this research project) or using OCPs for at least 3 months. We aim to include a similar number of women using OCPs as women not on OCPs in both the PCOS group and the control group.

Exclusion criteria for participation are psychiatric disorder, pregnancy or lactation, having undergone a hysterectomy (all indications), oophorectomy, or prolapse surgery, current or recent use of medications that are known to influence sexual response with the exception of OCPs, and (previous) medical disorders (other than PCOS) that are known to influence sexual response.

#### Sample Size Calculation

Considering the 5 primary outcome variables, we will apply Bonferroni correction, a 2-sided alpha of 0.01, and a power of 0.80.

ter Kuile et al reported differences between women with (N = 234) and without sexual problems (N = 108) on the FSFI and FSDS with effect sizes of, respectively, d = 1.9 and 2.3.^119^ For an effect size of d = 1.9, eight cases in each group are needed, and for an effect size of d = 2.3, 6 cases are required.

No data on the SDI are available for differences in women with PCOS. Strizzi et al^121^ reported an SDI of 38.1 (±16.56) in a sample of 29 women with a traumatic brain injury and a value of 49.59 (±21.09) in 29 normal controls, a difference of d = 0.60, suggesting that N = 67 cases for each group is required.

No data on VPA response in women with PCOS are available. However, there are VPA data available related to differences in premenopausal (N = 56) and postmenopausal (N = 32) women as reported by Both et al.^122^ In this study the difference in VPA response between premenopausal and postmenopausal women was reported as an F-value of 9.09 (degrees of freedom 1;84) corresponding to an effect size of n^2^ = 0.10 of d = 0.66. For such an effect 53 cases are needed in each group.

The largest sample needed is for the SDI; hence, we need 134 participants. Anticipating a small dropout of 10% we need 150 participants totally.

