#### Questionnaires

We will measure the following variables as primary outcomes (Table 1): sexual function with the FSFI total score (19 items, cutoff <26.55 indicative of sexual dysfunction)^101^; sexual distress with the FSDS-R total score (13 items, score >15 indicative of distress)^101^; and solitary and dyadic sexual desire with the SDI (14 items, 2 scales [solitary desire scale and dyadic desire scale] and total scale; a higher score reflects higher levels of sexual desire)^102^ as an additional measure of sexual desire due to limitations in the desire scale of the FSFI.^103^

**Table 1 tbl1:** Overview of primary and secondary outcome measures and independent variables

Outcome measures
Primary
Female Sexual Function Index
Female Sexual Distress Scale-Revised
Sexual Desire Inventory
VPA: genital sexual responsiveness
VPA: subjective sexual responsiveness
Secondary (mediators)
Sexual Esteem Scale
Rosenberg Self-esteem Scale
Body Image Self-consciousness Scale
The Multidimensional Body-Self-Relations Questionnaire-Appearance Scales
Hospital Anxiety and Depression Scale
Secondary (moderators)
Sexual and Physical Abuse Questionnaire
Sexual Excitation/Sexual Inhibition Inventory for Women
Revised Dyadic Adjustment Scale
Independent variables
PCOS status
OCP use

OCP = oral contraceptive pill; PCOS = polycystic ovary syndrome; VPA = vaginal pulse amplitude.

Other variables will be used as mediators (Table 1): sexual self-esteem measured by Sexual Esteem Scale (10 items, a higher total score indicates more sexual self-esteem)^49^^,^^104^; general self-esteem with the Rosenberg Self-Esteem Scale total score (10 items, a higher total score indicates more positive self-esteem)^105^, ^106^, ^107^; body self-consciousness with the Body Image Self-Consciousness Scale total score (15 items, a higher total score indicates greater body self-consciousness)^49^^,^^108^; body image with the Multidimensional Body-Self-Relations Questionnaire-Appearance Scales subscale (34 items, a higher total score indicates a more positive body image)^109^; and mental health with the Hospital Anxiety and Depression Scale total score (14 items, a higher total score indicates mental complaints).^110^^,^^111^

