### Statistical Analysis

Normality of the outcome data will be determined with Shapiro-Wilk tests. In case of non-normality, an appropriate transformation will be performed. The difference between women with PCOS and controls will be analyzed with separate multilevel regression analyses for each of the 5 outcomes. Independent variables will be PCOS (vs controls), fantasy (vs film), and vibration and interactions of PCOS with fantasy and vibration. *P* values of .01 will be considered significant.

For the differences between women with PCOS and controls, and women using OCPs and women not using OCPs, OCP use and interactions with PCOS, fantasy, and vibration will be added to the multilevel analyses.

Mediation regression analyses, as described by Mathieu and Tailor,^129^ will be extended to multilevel mediation regression analyses to estimate the mediating effects of steroid hormone levels, and sexual and psychosocial parameters in the relation of PCOS/OCP use on the 5 sexual outcome measures.

We will apply regression curve estimation with sexual function as the dependent variable and CAG repeat length and several functions of the CAG repeat length as independent variables to analyze a possible non-linear relation.

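### The 0.01 level protects 5% overall only with one PCOS test per primary outcome, but the plan allows 5 to 11 such tests

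*Protocol article*

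**What the plan says.** The Sample Size Calculation section sets the error rate: "Considering the 5 primary outcome variables, we will apply Bonferroni correction, a 2-sided alpha of 0.01, and a power of 0.80". Table 1 lists five primary outcomes: FSFI, FSDS-R, SDI, genital responsiveness and subjective responsiveness. The SDI appears there once.

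The Questionnaires section fixes one score for two of the instruments: "sexual function with the FSFI total score" and "sexual distress with the FSDS-R total score". For the third it gives several: "solitary and dyadic sexual desire with the SDI (14 items, 2 scales [solitary desire scale and dyadic desire scale] and total scale". It does not say which SDI score is tested.

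The Statistical Analysis section plans "separate multilevel regression analyses for each of the 5 outcomes" and gives the model terms: "Independent variables will be PCOS (vs controls), fantasy (vs film), and vibration and interactions of PCOS with fantasy and vibration". It then states that P "values of .01 will be considered significant", without limiting this to one term per model. OCP use and its interactions are added in a separate step, which the Background describes as a secondary, exploratory aim.

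**The concern.** A Bonferroni divisor must equal the number of tests on which a confirmatory claim may rest. Here the divisor counts outcomes, while the threshold is applied to models and instruments that can give more than one PCOS test per outcome. A PCOS effect could be declared on any of three SDI scores, or on any of three PCOS terms for each arousal outcome, and still be reported as protected by the correction.

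The interactions are not mere adjustment terms. The hypotheses in the Background expect stronger responses with higher androgen levels under fantasy and vibrotactile stimulation but not under visual stimulation, and the Sexual Response Assessment section orders the conditions for that reason. With 0/1 coding and film as reference (the coding is an assumption; the reference is as written), the PCOS coefficient is the group difference under film alone. Effects specific to fantasy or vibration would then appear in the interaction terms, so it is natural to expect claims to be made on them.

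**Working it through.** **Inputs.** From Sample Size Calculation: five primary outcomes, two-sided alpha 0.01, power 0.80, d = 0.60 and 67 per group for the SDI. From Questionnaires: one FSFI score, one FSDS-R score, two SDI scales plus a total. From Statistical Analysis: five models, threshold .01, and the terms PCOS, PCOS × fantasy and PCOS × vibration. The stimulus terms can apply only to the two arousal outcomes, because the questionnaires have no stimulus conditions.

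**The plan's own figures.**
- Per-test alpha: 0.05/5 = 0.01. Reproduced.
- Two-sample t-test, d = 0.60, two-sided alpha 0.01, power 0.80: 66.6, so 67 per group. Reproduced.

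**Possible test counts.**
- One test per outcome: 1 + 1 + 1 + 1 + 1 = 5.
- One PCOS term per arousal outcome, two or three SDI scores: 1 + 1 + (2 or 3) + 1 + 1 = 6 or 7.
- One SDI score, three PCOS terms per arousal outcome: 1 + 1 + 1 + 3 + 3 = 9.
- Two or three SDI scores, three PCOS terms per arousal outcome: 1 + 1 + (2 or 3) + 3 + 3 = 10 or 11.

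**Family-wise error for k independent tests at 0.01**, 1 − 0.99^k, with the bound k × 0.01 that holds under any dependence:

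| k | Independent | Bound |
|---|---|---|
| 5 | 4.90% | 5% |
| 6 | 5.85% | 6% |
| 7 | 6.79% | 7% |
| 9 | 8.65% | 9% |
| 10 | 9.56% | 10% |
| 11 | 10.47% | 11% |

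**Allowing for correlation.** PCOS terms within one model are correlated, and the SDI total contains its own scales. The documents give no correlations, so these are assumed: 0.3 to 0.7 between conditions within an arousal outcome, 0 to 0.5 between outcomes, and at least 0.4 between the two SDI scales. Simulating the test statistics with no PCOS effect anywhere gave 8.2% to 9.1% for 10 tests and 8.4% to 9.3% for 11. Five tests, one per outcome, gave 4.9% at correlation 0, 4.7% at 0.3 and 4.2% at 0.5.

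**If all 10 or 11 tests were kept as confirmatory.** The per-test alpha would be 0.05/10 = 0.0050 or 0.05/11 = 0.0045. At d = 0.60 and power 0.80 the t-test then needs 76 or 78 per group. Power at 67 per group would be about 73% or 72%.

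**The case against.** A reader might infer that the plan runs 10 to 11 primary tests and that its family-wise error is therefore about 10%. The article does not support that. Table 1 counts the SDI once, the Statistical Analysis section speaks of five outcomes, and the SDI calculation uses a single score per group. The list of SDI scales can be read as a description of the instrument. The interactions are listed as model terms and nowhere called primary, and the primary aim is worded as a difference between groups in each outcome. A figure of 10% also assumes independent tests, which these are not. All of this stands, and it limits the finding to a range.

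It can also be said that a condensed article may leave the choice of score and contrast to a full protocol or analysis plan. That would answer a complaint about missing detail only. The article itself states the divisor, the threshold, the model terms and the SDI scores, and these do not fit together: .01 applied to every PCOS term as written exceeds 5%, even with a single SDI score.

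Finally, Bonferroni is a valid method and the sample size is built on it consistently. That also stands. Holm is an improvement on offer and does not correct an error.

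**Conclusion.** The stated correction does not cover all the tests that the plan allows. The family-wise error is 4.9% with one PCOS test per outcome and rises to 10.5% with 11 independent tests. The middle case, with one SDI score and all three PCOS terms per arousal outcome, gives 8.65% under independence. For 10 or 11 tests, about 8-9% is more realistic than 10%, given the assumed correlations. Which figure applies depends on how many scores and terms are treated as confirmatory, and the article leaves that open. The 0.01 level and the SDI sample size are correct for five tests. The point should be settled before analysis, and the remedy is cheap.

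**What to change.** Name one confirmatory PCOS test for each outcome:
- FSFI: total score.
- FSDS-R: total score.
- SDI: one score, the one behind the d = 0.60 calculation.
- Genital response and self-reported arousal: one pre-chosen PCOS test each. This may be a joint test of the three PCOS terms, or one contrast that fits the stimulus-specific hypotheses. The PCOS difference averaged over all four conditions is another option, but it may dilute effects expected mainly under fantasy and vibration. The choice is the sponsor's.

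Label the other SDI scores and the individual PCOS terms secondary. The 0.01 level then holds, and 67 per group remains valid for the SDI. If a joint test is chosen for the arousal outcomes, its power should be checked separately, because the VPA calculation rests on a single two-group difference.

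Optionally, replace plain Bonferroni with Holm across the five tests at overall 0.05. The ordered P values are then compared in turn with 0.01, 0.0125, 0.0167, 0.025 and 0.05. This gives the same family-wise protection with at least as much power.

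The cost is a change of text and a decision on the arousal contrast, with no added participants. The remaining SDI scores and individual interaction terms lose confirmatory status, which is a scientific choice as well as an editorial one. The alternative of keeping all 10 or 11 tests confirmatory would need the lower per-test alpha and the larger groups shown in the working.

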### Materials and Measures

#### Blood Samples and Endocrine Screening

Peripheral venous blood samples to assess androgen levels will be collected in all participants: total testosterone, SHBG, and calculated free androgen index: testosterone × 100/SHBG. Additionally, all of the following will be assessed in all participants: estradiol, progesterone, luteinizing hormone, follicle stimulating hormone, androstedione, dehydroepiandrosterone, dehydroepiandrosterone sulfate, thyroid stimulating hormone, prolactin, lipids, and fasting glucose and insulin. Plasma will be stored at −80°C. Samples will be analyzed using liquid chromatography mass spectrometry.

We will determine the number of CAG repeats in 4 different ways: the number of CAG repeats in the allele containing the fewest CAG repeats (short allele), the number of CAG repeats in the allele containing the most CAG repeats (long allele), the mean number of CAG repeats (biallelic mean), and the number of CAG repeats in the active X chromosome based on X-inactivation analysis (X-weighted biallelic mean). The CAG repeat region in the first exon of the AR gene on the X chromosome will be amplified from genomic DNA with a polymerase chain reaction-based assay. Another possibility is to define single nucleotide polymorphisms that will detect the different variable number tandem repeat alleles and perform a less cumbersome Global Screening Array. We probably will take the latter approach to determine AR sensitivity.

The medical and endocrine screening as well as the DNA analysis for all participants will be done at 1 laboratory at Erasmus University Medical Center, to ensure compatibility of data.

#### Questionnaires

We will measure the following variables as primary outcomes (Table 1): sexual function with the FSFI total score (19 items, cutoff <26.55 indicative of sexual dysfunction)^101^; sexual distress with the FSDS-R total score (13 items, score >15 indicative of distress)^101^; and solitary and dyadic sexual desire with the SDI (14 items, 2 scales [solitary desire scale and dyadic desire scale] and total scale; a higher score reflects higher levels of sexual desire)^102^ as an additional measure of sexual desire due to limitations in the desire scale of the FSFI.^103^

**Table 1 tbl1:** Overview of primary and secondary outcome measures and independent variables

Outcome measures
Primary
Female Sexual Function Index
Female Sexual Distress Scale-Revised
Sexual Desire Inventory
VPA: genital sexual responsiveness
VPA: subjective sexual responsiveness
Secondary (mediators)
Sexual Esteem Scale
Rosenberg Self-esteem Scale
Body Image Self-consciousness Scale
The Multidimensional Body-Self-Relations Questionnaire-Appearance Scales
Hospital Anxiety and Depression Scale
Secondary (moderators)
Sexual and Physical Abuse Questionnaire
Sexual Excitation/Sexual Inhibition Inventory for Women
Revised Dyadic Adjustment Scale
Independent variables
PCOS status
OCP use

OCP = oral contraceptive pill; PCOS = polycystic ovary syndrome; VPA = vaginal pulse amplitude.

Other variables will be used as mediators (Table 1): sexual self-esteem measured by Sexual Esteem Scale (10 items, a higher total score indicates more sexual self-esteem)^49^^,^^104^; general self-esteem with the Rosenberg Self-Esteem Scale total score (10 items, a higher total score indicates more positive self-esteem)^105^, ^106^, ^107^; body self-consciousness with the Body Image Self-Consciousness Scale total score (15 items, a higher total score indicates greater body self-consciousness)^49^^,^^108^; body image with the Multidimensional Body-Self-Relations Questionnaire-Appearance Scales subscale (34 items, a higher total score indicates a more positive body image)^109^; and mental health with the Hospital Anxiety and Depression Scale total score (14 items, a higher total score indicates mental complaints).^110^^,^^111^

Some variables will be used as moderators (Table 1) as they are not caused by the independent variable (PCOS status): a history of sexual and physical abuse measured with Sexual and Physical Abuse Questionnaire (7 items, yes/no answers)^112^; sexual excitation and sexual inhibition propensity by Sexual Excitation/Sexual Inhibition Inventory for Women (36 items, 2 subscales, low Sexual Excitation Scale indicates low excitation, high Sexual Inhibition Scale indicates high inhibition)^113^; relationship satisfaction by Revised Dyadic Adjustment Scale total score (14 items, cutoff >48 for no distress).^114^^,^^115^

All questionnaires have been validated and will be available in a secure online environment.

#### Sexual Response Assessment

Sexual response will be assessed in 4 erotic stimulus conditions: 3-minute self-induced erotic fantasy, 2-minute vibrotactile glans clitoris stimulation, 5-minute erotic film, and 5-minute vibrotactile glans clitoris stimulation combined with an erotic film.^116^^,^^117^ Both erotic films depict heterosexual foreplay and intercourse. This film material has been previously used in studies from the same research group.^116^^,^^118^, ^119^, ^120^, ^121^ The short clips are taken from women friendly erotic films which are known to be effective in inducing a genital response. During the erotic fantasy condition, participants will be asked to fantasize about a pleasant sexual situation. The vibrotactile glans clitoris stimulation is provided by a small hands-off vibrator (2-cm diameter), attached to lycra panties. Vibrotactile glans clitoris stimulation has been used previously in studies on sexual response in women, and is known to elicit genital and subjective sexual arousal.^121^ The intensity of the vibration can be varied from very low^1^ to high.^10^ In the present study, high-intensity vibration will be provided. Each stimulus period is preceded by a 5-minute neutral film period, and followed by a 10-minute return-to-baseline interval during which participants will work on a non-erotic concentration task and watch a neutral film. A computer program coordinates the administration of the films and the vibrotactile glans clitoris stimulation.

All participants will go through the different stimulus conditions in the same order. Because sexual responses to erotic fantasy and vibrotactile glans clitoris stimulation are expected to differ according to androgen status, these 2 stimulus conditions are presented first, to avoid carry over from the visual stimuli that are known to be androgen independent and to elicit higher genital responses than fantasy and vibrotactile glans clitoris stimulation.^61^^,^^99^^,^^100^

Genital response will be measured using a vaginal photoplethysmograph assessing VPA.^122^, ^123^, ^124^ VPA is a sensitive, specific, and reliable measure of changes in vaginal vasocongestion in response to sexual stimulation^125^ and has been used in earlier studies in women with gynecological or neurological diseases.^120^^,^^126^ The vaginal device is sized and shaped as a vaginal tampon and can easily be inserted by the participant herself. It contains a light source and an optical sensor. The light source illuminates the capillary bed of the vaginal wall and the sensor responds to the light backscattered by the vaginal wall and the blood circulating within it. When the signal is connected to an alternating current amplifier, VPA is measured, which reflects the phasic changes in vaginal engorgement accompanying each heartbeat, with larger amplitudes reflecting higher levels of vaginal vasocongestion. Genital responses will be recorded continuously during the experiment. VPA will be averaged for the baseline condition and each erotic stimulus, and for each stimulus condition a change from the baseline score will be calculated. Ratings of self-reported sexual arousal and affect will be collected after each erotic stimulus. Participants will be asked to assess on a 7-point Likert scale their strongest feeling of sexual arousal.^127^^,^^128^

